## Abstract

Type 2 Diabetes Mellitus (T2DM) remains a global health challenge, with increasing prevalence in the Middle East, especially in Qatar. The Primary Health Care Corporation (PHCC) is the main provider of diabetes care in the country. Systematic evaluation through clinical audits provides a structured approach to identify gaps and improve clinical practices. This study aims to evaluate the effectiveness of clinical audit-based interventions in enhancing the management and documentation of T2DM in PHCC settings in Qatar. This quasi-experimental study will be conducted in three phases: pre-intervention, intervention, and post-intervention. In the pre-intervention phase, a cross-sectional situational analysis will be conducted across 31 PHCC health centers by reviewing 450 randomly selected patient records of adults diagnosed with T2DM. A baseline analysis will identify gaps in adherence to evidence-based diabetes care guidelines. The intervention phase will introduce specific quality enhancement strategies, which will encompass staff training, the distribution of guidelines, the engagement of audit champions, and various additional initiatives. Post-intervention, another 450 records will be audited to assess improvement. Additionally, 60 patients will be surveyed via telephone before and after the intervention to assess perceptions of care. The ICAE-DM CARE study aims to evaluate enhancements in clinical documentation, evaluation, and assessment of co-morbidities among patients with diabetes, alongside screening practices, adherence to evidence-based management protocols, and patient satisfaction levels. The findings will facilitate the institutionalization of audit-driven quality improvement initiatives within primary care settings. By providing robust evidence for integrating clinical audits into routine diabetes management, the study seeks to improve patient outcomes and support the objectives outlined in Qatar’s National Health Strategy.

## Introduction

Clinical audit is a well-established process for healthcare quality improvement and patient safety, particularly within hospital environments. It involves systematically reviewing care against explicit criteria, identifying gaps or areas for improvement, and implementing targeted changes to enhance patient outcomes [1]. The process offers numerous benefits, including improved patient care, demonstration of adherence to best practices, more efficient use of resources, increased patient satisfaction, professional development, and support for evidence-based practices [2]. Clinical audits can validate adherence to best practices and pinpoint areas for improvement, promoting transparency and continuous quality enhancement. [1,2].

The worldwide rise in type 2 diabetes mellitus (T2DM) is particularly alarming, with the highest prevalence rates recorded in the Middle East and North Africa at 9.3%, and Qatar exhibiting one of the most significant rates [3]. Projections indicate that by 2050, over 1.31 billion individuals will be diagnosed with diabetes, with prevalence rates surpassing 10%, especially in the Middle East and North Africa, where it is expected to reach 16.8%. This scenario highlights the urgent need for proficient management of diabetes within primary healthcare settings [3].

The application of clinical audits in managing chronic diseases such as type 2 diabetes has shown promising outcomes. For example, interventional audits have led to better management of glycemic levels and blood pressure, along with increased patient satisfaction [4]. Similarly, audits conducted within primary care settings have demonstrated significant improvements in guideline adherence and the appropriateness of diabetes screening and care [5,6]. These initiatives underscore the potential of clinical audits to identify deficiencies, guide targeted interventions, and promote sustained improvements in chronic disease management. In some cases, audits have prompted the development of specialized clinics and longer follow-up visits to ensure ongoing patient care and optimal outcomes [7,8].

Despite these favorable outcomes, there is a notable deficiency in studies investigating the repercussions of an entire audit cycle, particularly regarding chronic disease care, on clinical outcomes and documentation practices. The success of clinical audits largely depends on effectively implementing recommendations in healthcare settings [9]. However, organizational barriers such as limited collaboration between clinicians and management, unclear lines of authority, and differing perspectives can hinder progress. Overcoming these challenges requires fostering a collaborative environment and establishing clear accountability [10].

This study seeks to address a significant gap in literature by evaluating the impact of a systematic clinical audit process on the management and documentation of diabetes within primary care environments. Employing a framework that encompasses both pre- and post-intervention phases in alignment with the ICAE-DM CARE study protocol, this study will evaluate current practices, introduce targeted improvements, and examine the resulting outcomes. The aim is to determine the efficacy of clinical audits in enhancing diabetes care by analyzing variations in diabetes care process indicators, outcome indicators, and related documentation. The results are expected to provide critical insights into the contribution of systematic audit cycles to ongoing quality improvement initiatives. Since 2012, Qatar’s Primary Health Care Corporation (PHCC) has recognized clinical audits as an essential mechanism for ensuring clinical effectiveness, averaging 20–25 audits each year. However, the precise influence of these audits on the management of chronic diseases remains inadequately investigated. This study aims to evaluate the efficacy of clinical audits in improving diabetes care and documentation in accordance with PHCC standards, thereby offering substantial evidence regarding the importance of systematic review processes in enhancing chronic disease management. The study’s methodology, which includes pre- and post-analysis, interventions, and other components, is designed to be replicable across various primary healthcare settings.

## Methodology

### Study design and population

This study employs a mixed-methods approach, comprising a quasi-experimental design for cross-sectional data analysis and a cohort design for patient satisfaction surveys. The research will be conducted over a two-year period, from July 2025 to July 2027. Data will be extracted from the Electronic Medical Records (EMR) system of the Primary Health Care Corporation (PHCC), focusing on patients diagnosed with type 2 diabetes mellitus.

### Study settings

All 31 PHCC health centers providing diabetes care will be included. Data will be collected from stored electronic medical records and direct input from service users. The review of clinical guidelines will be conducted via online access to the PHCC intranet. Additionally, medical records will be reviewed through the Clinical Information System (CIS), and patient satisfaction will be assessed through structured telephone interviews.

### Study population

The study population includes adult patients (≥ 18 years) who are non-pregnant and have attended PHCCs for the management of type 2 diabetes within the past two years. Patients can be newly diagnosed or on follow-up.

**Inclusion Criteria:**

Age ≥ 18 yearsConfirmed diagnosis of type 2 diabetes mellitus, verified in the problem list or current diagnosis documentation.At least two clinical encounters at PHCCs within the last two yearsAbility to communicate verbally via telephone and provide informed verbal consent

**Exclusion Criteria:**

Pregnant womenPatients with encounters solely for medication refills without additional clinical dataPatients below 18 years of agePatients unable to communicate by phone or unable to provide verbal consent

### Data collection procedures

Data variables pertinent to the study objectives will be retrieved from the PHCC EMR system, including demographic information, diagnostic details, clinical encounters, and healthcare utilization patterns.

### Telephonic interviews

For qualitative insights and patient satisfaction assessment, eligible patients will be contacted via telephone. The telephonic interview will follow the same inclusion and exclusion criteria, emphasizing the ability to communicate by phone and give verbal consent. Interviews will be conducted by trained personnel, ensuring confidentiality and adherence to ethical standards. Verbal informed consent will be obtained prior to interviews.

This methodological framework allows for comprehensive analysis of clinical data and patient perceptions, facilitating a robust assessment of diabetes management within the primary care setting.

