### Sample selection

A stratified simple random sampling method will be employed to select representative samples for both the cross-sectional and cohort components of the study. For the cross-sectional analysis, a total of 450 patient records will be randomly selected from the medical records department across 31 health centers. This sample size was calculated based on a 5% margin of error, a 95% confidence interval, and an assumed response distribution of 50%, with an additional allowance for potential non-responses. The selection will take place at two different time points: baseline and post-intervention, with 450 cases reviewed at each stage to facilitate a comparative analysis of diabetes-related encounters over the preceding three months.

For the patient satisfaction component, a subset of 60 patients will be randomly selected at each time baseline and post-intervention—from the larger cohort. These patients will be contacted by telephone to complete satisfaction surveys, offering qualitative insights into their perceptions of care. The randomization process will be independently applied at both time points to ensure comparability and minimize selection bias. A sample size of 60 patients per time point is considered sufficient to balance feasibility with the need for meaningful analysis of patient satisfaction trends. This approach ensures the robustness and reliability of findings and supports a comprehensive evaluation of both clinical outcomes and patient perspectives throughout the intervention period.

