### Patient satisfaction survey

A structured telephone-based patient satisfaction survey will be conducted with a sub-sample of patients. The survey is based on key performance indicators (KPIs) aligned with PHCC clinical practice guidelines for diabetes management. This tool was developed and validated by the Department of Clinical Effectiveness to ensure relevance and reliability in measuring patient experience.

Survey data will be recorded using a secure Excel spreadsheet preformatted with all measurement parameters. *(see*
Table 2
*for Patient Satisfaction Questionnaire).*

**Table 2 pone.0313664.t002:** Patient Satisfaction Survey Indicators.

Question	Indicator
Q1	Did your doctor inquire about and discuss diabetes-related signs and symptoms?
Q2	Did your doctor request any new blood tests or referrals?
Q3	Did your doctor explain how to monitor blood sugar and what to do in case of high/low readings?
Q4	Did your doctor provide advice about diet and physical activity?
Q5	Did your doctor set an HbA1c goal and discuss your treatment plan?
Q6	Overall, are you satisfied with the care provided during your visit?

Source: PHCC clinical practice guideline for the management of Type 2 Diabetes.

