### Intervention and follow-up

Following the initial cross-sectional analysis, identified gaps in care quality and patient satisfaction will inform the development of a comprehensive action plan. This plan will be implemented across all participating health centers to address the deficiencies and enhance service delivery. The intervention will be embedded into standard auditing procedures to ensure continuous quality improvement.

The intervention phase will last approximately 8–9 months. Afterward, a second round of data collection will be conducted using the same methodology and variables to ensure consistency and enable direct comparison. This approach will support the evaluation of changes in clinical performance and patient experience before and after the intervention *(see*
Fig 1
*for the study flow chart).*

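### The two-year survey eligibility rule and the three-month encounter window are not reconciled, so round 2 may include patients not seen since the intervention began

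*Protocol article*

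**What the plan says.** Survey eligibility is stated in one place, the Telephonic interviews section of the protocol article: "The telephonic interview will follow the same inclusion and exclusion criteria". Study population describes these patients as people who "have attended PHCCs for the management of type 2 diabetes within the past two years", and the Inclusion Criteria ask for two or more PHCC encounters in the same period. No inclusion or exclusion criterion asks for a visit during or after the intervention.

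Sample selection brings in a second window. At each stage 450 cases are reviewed "to facilitate a comparative analysis of diabetes-related encounters over the preceding three months". The next paragraph says that "a subset of 60 patients will be randomly selected at each time baseline and post-intervention—from the larger cohort" and that "The randomization process will be independently applied at both time points". It does not say which group the larger cohort is.

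On timing, Intervention and follow-up states "The intervention phase will last approximately 8–9 months" and puts the second data collection after it. Evaluation of audit impact places the post-intervention phase 8–9 months after implementation.

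Table 2 lists six survey questions. Only question 6 refers to a visit: "Overall, are you satisfied with the care provided during your visit". Questions 1–5 ask whether the doctor did something and name neither a visit nor a period.

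**The concern.** Under the two-year rule, a patient last seen more than nine months before round 2 meets every written criterion for the post-intervention survey but can describe only care given before the intervention. Such respondents should answer much as a baseline respondent would, so they pull the before-after difference toward zero. A real improvement in patient-reported care would look smaller than it is.

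The questionnaire does not protect against this. A respondent with several visits, some before and some after the intervention began, is not told which one to report.

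The survey is the study's only patient-reported measure and has 60 respondents per round, so it has little precision to spare.

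**Working it through.** **Plan's own figure.** The survey size of 60 per round is given without an effect size, power or precision, so there is no calculation to reproduce.

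**Step 1: the two readings.**
- *Reading A, the eligibility text.* Telephonic interviews points to the general criteria: two or more encounters in 24 months, with no condition on recency. Patients last seen before the intervention qualify for round 2.
- *Reading B, the sampling text.* The 60 are a subset of that round's 450 audited cases, and each audited case has an encounter in the preceding three months. Round 2 comes 8–9 months after implementation, so that encounter cannot precede the intervention. The unexposed share is zero.

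The text does not settle the choice. The three-month window describes what the records are compared on and is not written as an eligibility rule. The source of the 60 is undefined. Study design and population uses the word cohort for the satisfaction survey and calls the record data cross-sectional, so a larger cohort is not clearly the 450 audited records.

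**Step 2: the unexposed share under reading A.** Inputs from the article: a 24-month window and an intervention of m = 8 or 9 months. Assumptions not in the article: k encounters fall independently and uniformly over the 24 months, and round 2 starts when the intervention phase ends. The share with no encounter since the intervention began is

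f = ((24 − m)/24)^k

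| Encounters k | m = 9: (15/24)^k | m = 8: (16/24)^k |
|---|---|---|
| 2 | 0.391 | 0.444 |
| 4 | 0.153 | 0.198 |
| 6 | 0.060 | 0.088 |
| 8 | 0.023 | 0.039 |

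A later start of round 2 would make m larger and every share smaller.

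**Step 3: effect on the difference.** If unexposed respondents answer as at baseline, observed change = (1 − f) × true change. For an assumed true change of 20 points:
- two encounters: 20 × (1 − 0.444) = 11.1 to 20 × (1 − 0.391) = 12.2 points
- four: 20 × (1 − 0.198) = 16.0 to 20 × (1 − 0.153) = 16.9 points
- six: 20 × (1 − 0.088) = 18.2 to 20 × (1 − 0.060) = 18.8 points
- eight: 20 × (1 − 0.039) = 19.2 to 20 × (1 − 0.023) = 19.5 points

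**Step 4: against the survey's precision.** With 60 per round and a proportion of 0.5, the 95% half-width for a difference between two independent rounds is 1.96 × √(0.5/60) = 17.9 points. For an assumed rise from 60% to 80%, take power = Φ{[Δ − 1.96√(2p̄(1 − p̄)/60)] / √[(p₁q₁ + p₂q₂)/60]}, with two-sided alpha 0.05. Power is then 67% at f = 0, 60% at f = 0.07, 50% at f = 0.17 and 27% at f = 0.42. The rates and the values of f are illustrative; the article gives neither.

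**The case against.** The best reply is reading B. The sentence on the 60 follows directly on the one about 450 cases and three months, it calls the 60 a subset, and the Patient satisfaction survey section calls them a sub-sample. Read together, these make it natural to draw respondents from that round's audited cases, and then there is no dilution from this source. Nor do the windows strictly contradict each other: two encounters in two years can define an established patient, and three months can pick the encounter to be assessed. Both points stand as possible readings. However, the article does not state this one, and a team that follows the survey's own eligibility sentence would draw a different sample.

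The size is also open to challenge, and rightly. A reader might infer that about 40% of round-2 respondents would be unexposed. That requires every respondent to have exactly two uniformly timed encounters, whereas the criterion sets two as a minimum. Criterion 7 in Table 1, a follow-up HbA1c 3–6 months after treatment initiation, suggests more contacts for the patients it covers, and patients seen solely for refills are excluded.

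A reader might also infer that the survey cannot show post-intervention experience at all. That does not follow: even in the two-encounter case, 56–61% of respondents would have been seen since the intervention began. Nor do all the questions ask about one visit; only question 6 does.

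Finally, interviewer scripts and dated prompts often sit in a survey manual, and their absence from an article is no fault. What remains is that the article prints the questions and the eligibility rule, and these leave open which encounter is being rated.

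**Conclusion.** The point holds as an unreconciled specification, not as proof that the survey will enrol unexposed patients. The eligibility text admits round-2 respondents not seen since the intervention began. The sampling text can be read to exclude them, but does not say so. If they are included, the bias is toward zero, provided that they answer as at baseline.

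Its size cannot be taken from the document, because visit frequency is not given. Under uniform visits and a round 2 that follows directly on the intervention, the unexposed share runs from 39–44% (two encounters) down to 2–4% (eight). Under the three-month reading it is zero. The missing index visit in Table 2 is a smaller, related weakness that remains under either reading for patients with more than one visit.

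**What to change.** Reconcile Study population, Inclusion Criteria, Telephonic interviews and Sample selection with one statement: in each round the 60 respondents are drawn from that round's audited cases with a diabetes-related encounter in the preceding three months, and in round 2 that encounter falls after implementation at the patient's centre. Replace the undefined larger cohort with this definition. The two-year criterion can stay as the description of an established patient. Tie all six questions in Table 2 to that encounter, with the same wording in both rounds.

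The cost is protocol wording and one date filter on the record sampling frame, and 450 audited cases per round is a workable source for 60 interviews. The downside is a frame that favours recent attenders. This should be stated as a limit on whom the survey represents; because the same three-month rule applies in both rounds, the comparison stays like with like in this respect.

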### Sample selection

A stratified simple random sampling method will be employed to select representative samples for both the cross-sectional and cohort components of the study. For the cross-sectional analysis, a total of 450 patient records will be randomly selected from the medical records department across 31 health centers. This sample size was calculated based on a 5% margin of error, a 95% confidence interval, and an assumed response distribution of 50%, with an additional allowance for potential non-responses. The selection will take place at two different time points: baseline and post-intervention, with 450 cases reviewed at each stage to facilitate a comparative analysis of diabetes-related encounters over the preceding three months.

For the patient satisfaction component, a subset of 60 patients will be randomly selected at each time baseline and post-intervention—from the larger cohort. These patients will be contacted by telephone to complete satisfaction surveys, offering qualitative insights into their perceptions of care. The randomization process will be independently applied at both time points to ensure comparability and minimize selection bias. A sample size of 60 patients per time point is considered sufficient to balance feasibility with the need for meaningful analysis of patient satisfaction trends. This approach ensures the robustness and reliability of findings and supports a comprehensive evaluation of both clinical outcomes and patient perspectives throughout the intervention period.

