### Medical record review

The medical record review will be conducted by experienced clinical auditors trained in assessing adherence to evidence-based diabetes management guidelines. Data will be systematically recorded using a customized Excel spreadsheet developed specifically for this study, containing all predefined audit criteria.

The review will focus on newly diagnosed type 2 diabetes mellitus (T2DM) patients, particularly those with an HbA1c value ≥6%, to assess whether appropriate clinical services and interventions were delivered in line with guideline recommendations.

The collected data will allow a comprehensive evaluation of healthcare provider adherence, identifying gaps in clinical care and informing quality improvement initiatives across PHCC settings. *(see*
Table 1
*for data collection variables).*

**Table 1 pone.0313664.t001:** Clinical Audit Criteria and Variables.

Criterion	Description
Criterion 1	ASCVD risk assessment for all adult patients (≥40 years) at diagnosis
Criterion 2.1	Laboratory Investigations: HbA1c, lipid profile (TC, HDL, LDL, TG), serum creatinine and eGFR, liver function (ALT, AST), urine albumin/creatinine ratio, TSH (if dyslipidemia or female >50 years), urine ketones (if glucose >250 mg/dL), serum potassium (if on ACEi/ARB/diuretics)
Criterion 2.2	Initial general foot examination
Criterion 2.3	Referral to eye specialist for initial retinal assessment
Criterion 3	Documentation of HbA1c target goals
Criterion 4	Appropriate treatment initiated or adjusted based on guidelines
Criterion 5	Patient education on diet and physical activity at initial visit
Criterion 6	Referral to dietitian for Medical Nutrition Therapy (MNT)
Criterion 7	Follow-up HbA1c test ordered within 3–6 months from treatment initiation

Source: PHCC clinical practice guideline for the management of Type 2 Diabetes.

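### The three-month look-back, the focus on newly diagnosed patients and Criterion 7's 3–6 month follow-up window do not fit together, so Criterion 7 needs its own index window in both rounds

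*Protocol article*

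**What the plan says.** The relevant statements are all in the Methodology of the protocol article.

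- **Sample selection:** 450 records are reviewed at baseline and 450 after the intervention, "to facilitate a comparative analysis of diabetes-related encounters over the preceding three months".
- **Medical record review:** "The review will focus on newly diagnosed type 2 diabetes mellitus (T2DM) patients". No time limit is attached to that term.
- **Table 1:** some items are tied to the start of care. Criterion 1 is "ASCVD risk assessment for all adult patients (≥40 years) at diagnosis" and Criterion 5 is "Patient education on diet and physical activity at initial visit". Criterion 7 is tied to a later period: "Follow-up HbA1c test ordered within 3–6 months from treatment initiation".
- **Study population and Inclusion Criteria:** eligibility spans two years, needs at least two encounters, and is broad: "Patients can be newly diagnosed or on follow-up".
- **Intervention and follow-up:** "The intervention phase will last approximately 8–9 months". The second round then repeats the first with the same method and variables.

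**The concern.** Criterion 7 is the only one of the nine audit items that measures follow-up. It can be judged as missed only once six months have passed since treatment began. The printed look-back is three months, and the article does not say how the two are to be combined.

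Two things are at stake. First, baseline gaps drive the action plan at all participating centers. If open windows are scored as failures, adherence is biased downward and the plan may chase a gap that reflects only short follow-up. Second, the same method is used again in the second round. Any artefact returns there, by an amount that depends on the mix of follow-up times in each round. If older patients are used instead, part of what is scored as post-intervention care was delivered before the intervention, and the pre/post contrast on this item is diluted.

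**Working it through.** **The plan's own calculated figure.** Sample selection gives a 5% margin, 95% confidence and a 50% proportion: n = 1.96² × 0.25 / 0.05² = 384.1, rounded up to 385. The non-response allowance is not stated. At an assumed 15%, 385/0.85 = 453 or 385 × 1.15 = 443, so 450 is reproduced approximately. The concern does not depend on this figure.

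**Inputs from the article.** Look-back 3 months; Criterion 7 window from month 3 to month 6 after treatment start; eligibility 24 months; intervention 8–9 months (midpoint 8.5).

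**Assumptions.** Treatment starts are spread evenly over the period considered. The second audit falls at the end of the intervention; Evaluation of audit impact places it 8–9 months after implementation.

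**Reading (a): treatment started inside a look-back of L months.** The share past month 3 is max(0, (L − 3)/L). The share with a closed window is max(0, (L − 6)/L).

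| L (months) | past month 3 | window closed |
|---|---|---|
| 3 | 0% | 0% |
| 6 | 50% | 0% |
| 9 | 66.7% | 33.3% |
| 12 | 75% | 50% |
| 24 | 87.5% | 75% |

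At the printed L = 3, no window has opened, let alone closed.

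**Reading (b): starts anywhere in the 24 months before the second audit.** A patient who started s months before the audit has a Criterion 7 window running from s − 3 to s − 6 months before it. The intervention began 8.5 months before it.

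- Closed window: s ≥ 6, which is 24 − 6 = 18 months of starts, or 18/24 = 75%.
- Closed and wholly inside the intervention: s − 3 ≤ 8.5, so s runs from 6 to 11.5. That is 5.5 months: 5.5/24 = 23% of starts and 5.5/18 = 31% of closed windows.
- Straddling the start of the intervention: s from 11.5 to 14.5. That is 3 months: 3/18 = 17% of closed windows.
- Wholly before the intervention: s − 6 ≥ 8.5, so s from 14.5 to 24. That is 9.5 months: 9.5/18 = 53% of closed windows.
- At least partly inside: (5.5 + 3)/24 = 8.5/24 = 35% of starts.

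Over the stated range, an 8-month intervention gives 5/24 = 21% of starts wholly inside and 10/18 = 56% of closed windows wholly before. A 9-month intervention gives 6/24 = 25% and 9/18 = 50%.

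Under reading (b) the diagnosis and first-visit items of these same patients fall outside the three months of encounters. So neither reading lets the printed window serve every criterion for one patient.

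**The case against.** A reader might infer that Criterion 7 can never mature, or cannot be validly scored in either round. The article does not support that. The look-back limits encounters, not dates of diagnosis or treatment start. Follow-up patients are admitted over two years, and Evaluation of audit impact describes open chart review, so earlier entries are not barred. A patient who started treatment some months ago and attended recently can be audited. At baseline no exposure condition applies, and under even starts over 24 months 75% have a closed window. The 0% therefore holds only if treatment must have started inside the look-back.

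The criterion also concerns an order. An order placed ahead might count, and the wording does not settle it. This would let some patients pass early, but it would not make a missing order a failure before month 6.

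The audit spreadsheet is not shown and may hold a not-yet-due code, so it cannot be said that auditors will mark such patients as failed. What remains is that the three-month window, the newly diagnosed focus and the 3–6 month criterion are all printed in the article and conflict there.

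A reader might also count only patients who started treatment under the intervention and have a closed window, (8.5 − 6)/24 = 10%. That is too strict. The item concerns ordering in months 3 to 6, so the place of that window matters, which gives 23% wholly inside or 35% at least partly inside.

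**Conclusion.** The concern holds as a conflict between printed statements that must be reconciled before extraction. On the narrow reading, 0% of audited patients have a closed Criterion 7 window. On the wide reading the item can be scored, but 53% of closed windows in the second round lie wholly before the intervention, and 23% of starts have a closed window wholly inside it.

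The wide-reading figures rest on even starts over 24 months, an 8.5-month intervention and an audit at its end. Eligibility limits encounters rather than starts, so patients with still older starts would make the dilution worse. A stronger focus on recent diagnoses would lessen it, but would leave more windows open.

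Severity is moderate. One of nine criteria is affected, and the article names no primary endpoint that rests on it.

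**What to change.** Reconcile Sample selection with Medical record review and Table 1:

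1. Define newly diagnosed by a date limit, and state the index date from which each criterion is read.
2. Give Criterion 7 its own index window, identical in both rounds: patients who started treatment at least 6 months before extraction, for example 6 to 11.5 months. The 3–6 month window is then closed and, in the second round, lies within an 8.5-month intervention. Adjust the upper limit to the actual length (intervention plus 3 months).
3. Class open windows as not yet due and leave them out of the denominator. State whether an order placed before month 3 counts.
4. Keep the three-month window for the other criteria.

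**Cost.** The denominator for this item shrinks, or a separate draw of records is needed. If the 450 records had even starts over 24 months, about 450 × 5.5/24 = 103 would qualify per round. The 95% half-width at 50% would be 1.96 × √(0.25/103) = 9.7 percentage points, against 1.96 × √(0.25/450) = 4.6 with all 450 (simple random sampling). The precision for Criterion 7 should be stated on its own denominator. If the main sample is restricted to recent starts, a date filter on those records is not enough and other records must be drawn.

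Reading the second-round records later instead is not a sound alternative. For treatment started in the last three months of the intervention, months 3 to 6 fall after the intervention phase has ended.
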